##### **9.1.6.Inter-observer reproducibility**

### **9.2. Number of participants to be included in this study and statistical justification**

The necessary number of participants was calculated to answer the main objective of the study: determine if there is relationship between stress and performance.

To determine if there is a relationship between stress and performance, such that the correlation coefficient will attain a value of at least 0,50, with type I error at 5 % and power at approximately 90%, using a bilateral test, the number of subjects to be included is calculated to be 48 (Proc POWER, SIEVE). Our study will include 12 teams of 4 persons each, and each team will include representatives from four status categories (a senior physician, a junior physician (resident ["interne"]), a nurse and an ambulance driver.

To answer secondary objectives, the teams will be distributed in 2 randomised groups, 1 and 2.

It is noteworthy that in a previous study, a sample size of 12 participants each of the professional categories allowed for finding a difference of 2,1 points on an IO access evaluation scale of 20 points (Oriot 2012), knowing that the standard deviation of this score was described to be 1,02 in a previous study.

On the other hand, there is lack of sufficient information in the literature with regard to the number of subjects necessary to determine if there is a difference in the variability of various scores. The power of our study for questions corresponding to secondary objectives will thus be calculated *a posteriori* from the data actually observed.

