### 3. STUDY OBJECTIVES

#### 3.1. Primary objective

**To seek evidence for the existence of stress**, as it will be assessed by three processes throughout the various scenarios:

- Biological stress (Salivary Cortisol [SC]);
- Electrophysiological stress (Holter 24h, timely measures);
- Psychological stress.

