### 4. STUDY DESIGN

#### 4.1. Primary outcome measures

Our primary outcome measure will consist of revealing and evaluating evidence for the existence of stress during the simulation. Such stress will be estimated by 3 different methods:

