### **9.3. Degree of statistical significance**

A *p* score < 0.05 will be considered as statistically significant

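### The stated primary objective, existence of stress, has no test, no decision rule and no sample-size basis, because Section 9.2 sizes the trial for a different main objective

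*Protocol*

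**What the plan says.** Protocol Section 3.1 gives the primary objective as "To seek evidence for the existence of stress", assessed biologically, electrophysiologically and psychologically. Section 4.1 repeats it: "Our primary outcome measure will consist of revealing and evaluating evidence for the existence of stress during the simulation". It then lists salivary cortisol; Holter heart rate, pNN50 and LF/HF; spot heart rate and blood pressure; and STAI, SOM, IES-R and PCLS. Section 3.2 makes performance, and the effect of repeated sessions, secondary.

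Section 9.2 starts from a different place: "The necessary number of participants was calculated to answer the main objective of the study: determine if there is relationship between stress and performance". The effect to be detected is put as follows: "the correlation coefficient will attain a value of at least 0,50". The error rates are given as "type I error at 5 % and power at approximately 90%, using a bilateral test". From these inputs the section concludes that "the number of subjects to be included is calculated to be 48". The structure follows: "Our study will include 12 teams of 4 persons each".

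Section 9.1 plans a stress-performance correlation (9.1.2), repeated-measures tests of performance scores (9.1.3), a comparison of performance change between groups 1 and 2 (9.1.4), and a comparison of stress markers between groups 1 and 2 (9.1.5). Section 9.3 adds one general rule, a p "score < 0.05 will be considered as statistically significant".

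**The concern.** The protocol names two different main questions, and its only prospective sample size belongs to the one that Sections 3.1 and 3.2 do not list as an objective at all. The question called primary is given neither an effect size nor an analysis. Followed as written, the trial would finish without a test of its primary objective, and whoever reports it would have to choose the variable, the baseline and the success criterion after seeing the data. With several markers measured at several times, that choice can turn a chance result into the headline conclusion.

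**Working it through.** **1. The plan's own figure.** Inputs from Section 9.2: r = 0.50, two-sided 5%, power about 90%. By Fisher z, N = ((1.960 + 1.282) / atanh(0.50))² + 3, with atanh(0.50) = 0.549. This gives N = 37.8, so 38 rather than 48. With 48, power = Φ(0.549 × √45 − 1.960) = Φ(1.725) = 96%. The stated 48 does not follow from the stated inputs, although the difference is conservative if people are independent. In any case the calculation concerns a correlation and says nothing about whether stress exists.

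**2. Matching each planned analysis to the primary objective.**

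| Section | Analysis | Tests existence of stress? |
|---|---|---|
| 9.1.1 | Descriptive summaries | No test |
| 9.1.2 | Correlation of stress with performance | No; association only |
| 9.1.3 | ANOVA or Friedman on performance scores; mixed model only as a possibility | No |
| 9.1.4 | Group 1 vs 2, performance change | No |
| 9.1.5 | Group 1 vs 2, stress markers | No; Sections 4.3.7 and 9.2 tie the two groups to the secondary objectives |

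Nothing uses the day-before or just-before measurements as a baseline, although Section 4.4.1 schedules both for cortisol, Holter, blood pressure, heart rate and STAI.

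**3. Size of the decision-rule gap.** Counting each item in Section 4.1 gives ten variables: cortisol 1, Holter 3, spot measures 2, questionnaires 4. Leaving out either the spot measures or the two later questionnaires (IES-R, PCLS) gives eight. If any one result at 5% sufficed and the tests were independent, the family-wise error would be 1 − 0.95^k:

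- k = 3 methods: 14%
- k = 8 variables: 34%
- k = 10 variables: 40%

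The markers are surely correlated, and the documents give no correlations. Simulating ten equally correlated tests gives about 35%, 29%, 21% and 13% at assumed correlations of 0.3, 0.5, 0.7 and 0.9. If all markers had to be significant, there would be no inflation.

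**4. The correlation family.** Section 9.1.2 names cortisol, Holter parameters and stress-scale scores (1 + 3 + 4 = 8) against the global, IO insertion and teamwork scores (TAPAS, IOPAS, BAT, CTS = 4). That is 8 × 4 = 32 pairs, so 32 × 0.05 = 1.6 false positives expected under the null, before subgroups and time points.

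**5. What 48 people could support for the stated primary objective.** Take a within-person contrast at two-sided 5% with 90% power; the effect is in SDs of the within-person change.

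- People independent, 47 df: the required noncentrality is 3.31, and 3.31 / √48 = 0.48 SD.
- Teams as clusters of four, 11 df: the required noncentrality is 3.57, and the detectable change is 3.57 × √((1 + 3 × ICC) / 48). An assumed ICC of 0.1 gives 0.59 SD, and 0.2 gives 0.65 SD.

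The protocol gives no ICC, so these two values are assumptions.

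**The case against.** The strongest reply is that the protocol's real question is stress and performance. The title, the expected results, Section 6.1 and Section 9.2 all point that way, and Section 6.1 treats evidence of stress as the first part of estimating its effect on performance. That stands as a reason not to presume which question should be primary. It does not remove the conflict with Sections 3.1 and 4.1.

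A second reply is that multiplicity handling and the exact contrast are commonly left to a statistical analysis plan, which is not at hand. This also stands in part: the missing adjustment alone would not be a finding. But a later plan cannot reconcile two contradictory statements of the main objective without overriding one of them, and Section 9.1 does assign tests to the secondary questions.

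A reader might go further and infer that each of about ten markers will be tested at 5% and that any one success proves stress, giving a 40% error rate. The documents do not support that. Section 9.3 attaches its threshold to no primary test, no any-one rule is stated, and 40% also needs independence, which is implausible for several cardiac measures. Nor does Section 9.1.2 support 60 correlations (ten stress variables by six performance measures) or 180 across three populations. It does not name blood pressure, spot heart rate or the IO timing variables, and the three populations are the whole sample and its two halves.

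**Conclusion.** The contradiction is firm and needs no assumption: Sections 3.1 and 4.1 name one primary question, Section 9.2 sizes another, and Sections 9.1.2 to 9.1.5 contain no test of the first. The stated primary objective therefore has no analysis, no decision rule and no sample-size basis. This must be settled before the data are analysed.

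The error-rate figures only illustrate what an any-one-suffices reading would cost: about 14% to 40% under independence, depending on the count, and about 13% to 35% for ten tests at the assumed correlations. They do not describe a rule in the protocol. The detectable changes of 0.59 to 0.65 SD rest on the assumed ICCs and on 11 team-level degrees of freedom.

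**What to change.** Make Sections 3.1, 4.1 and 9.2 name the same primary question.

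- **If existence of stress stays primary:** prespecify one variable and one within-person contrast from data already collected. Salivary cortisol after simulation against a stated baseline is one example, not the only option. Choose between the day-before and just-before samples and give the reason, since Section 7.3.2 puts the former at about 18H00 and the sessions between 14H00 and 15H00. Alternatively, state a rule across the three methods, such as all required, or Holm. Analyse with a random team effect, and add to Section 9.2 the change detectable with 48 people in 12 teams, with the ICC labelled as an assumption.
- **If stress-performance is the intended primary question:** amend Sections 3.1 and 4.1, name one stress variable and one performance score, and rework the Section 9.2 calculation, which does not give 48 from its own inputs and ignores the teams.

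In either case, label the remaining markers and correlations secondary, with multiplicity control or reported as estimates with confidence intervals.

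The cost is protocol wording and a short analysis paragraph, with no new data or participants. The downside is that the other markers lose confirmatory status.

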#### 4.2. Secondary outcome measures

##### 4.2.1. Evaluation of performance

**Team performance** of a simulated infant shock management will be assessed by three ways:

- **Global team clinical performance** will be evaluated using performance assessment scale ("TAPAS"), designed by the Simulation Laboratory and in validating process (Oriot 2013, unpublished data).
- **IO access procedure process and success** of the insertion technique: evaluated by
  - An assessment scale - IOPAS - *Intraosseous Performance Assessment Scale* (Oriot 2012),
  - Time to decision,
  - And duration of procedure (Oriot 2012) (cf. Appendix).
- **Teamwork performance** will be evaluated using the following validated scales:
  - concerning **Leadership assessment**: BAT – *Behavioural Assessment Tool* (Anderson 2010) (cf. Appendix)
  - concerning **Global Teamwork assessment**: CTS - *Clinical Teamwork Scale*, CTS (Guise 2008) (cf. Appendix)

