#### **4.3.4.Supervisors and evaluation**

Two independent supervisors at a time will evaluate each simulation session of the Sim-Stress research protocol.

These supervisors, who are members of the University Hospital of Poitiers

(CHU de Poitiers) Simulation Laboratory, will be chosen in random manner. They each have different specialities, and are all simulation trainers, qualified in performing debriefing sessions.

This team of supervisors will consist of [name] (pediatric intensivist), [name] (pediatric emergency physician), [name] (surgical intensivist), [name] (adult emergency physician), and 4 emergency or pediatric fellows. They will analyze global performance with the respect to algorithm, IO access performance and global teamwork - leadership and communication. The mean between the two supervisors' scores will be used as the reference value. Interobserver reproducibility will be calculated according to the scale used.

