##### 4.4.2.2. Number of team simulation sessions:

Participants of group 1: 6 teams x 9 sessions = 54 simulation sessions

Participants of group 2: 6 teams x 3 sessions = 18 simulation sessions

TOTAL = 54 + 18 = 72 team stimulation sessions

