##### **9.1.2.Evaluation of the effect of stress on performance**

The relationship between

- The various variables and indicators of stress (salivary cortisol concentration, Holter parameters of, scores from the various stress scales) evaluated during the 1-st session (basal stress) and during the following sessions,
- And performance (global performance, IO insertion and teamwork evaluation scores), evaluated during the latter sessions,

will be studied by calculating a Pearson correlation coefficient (or Spearman correlation coefficient if need be). This calculation will be realized on the entire study population as well as within each of the groups 1 and 2. A search for any sort of heterogeneity based on status (senior physician, junior physician, nurse, ambulance driver) will be undertaken, as well.

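### Section 9.2's 90% power for r = 0.50 counts 48 participants as independent pairs, but performance is scored per team, so power rests on 12 teams and on an unstated level of r

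*Protocol*

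**What the plan says.** Protocol section 9.2 sizes the study to "determine if there is relationship between stress and performance". The effect it sets out to detect is described by the words "such that the correlation coefficient will attain a value of at least 0,50". The test is two-sided at the 5% level and the target power is about 90%. From this the section concludes that "the number of subjects to be included is calculated to be 48". It then describes these 48 as 12 teams of four, with no allowance for grouping. It is the only power figure in the protocol, because power for the secondary objectives is deferred to calculation from the observed data.

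Section 9.1.2 gives the matching analysis. The relationship between stress and performance "will be studied by calculating a Pearson correlation coefficient (or Spearman correlation coefficient if need be"), on the whole population, within each group, and with a search for differences by professional status.

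The two variables sit at different levels. Section 7.2 has stress estimated for every participant. Section 4.2.1 says that team performance "of a simulated infant shock management will be assessed by three ways", covering the global scale, IO access, and teamwork with leadership. In section 4.3.4 two supervisors rate each simulation session, and "The mean between the two supervisors' scores will be used as the reference value". Section 4.4.2.2 counts "6 teams x 9 sessions = 54 simulation sessions" for Group 1 and 18 for Group 2, or 72 team sessions.

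**The concern.** At any one session there are 48 stress values but only 12 performance values on each scale. If 48 rows are correlated, each team's score appears four times, and the usual test treats the copies as separate information.

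Two things are at stake. The stated power may not be what the design delivers for the question that 9.2 calls the main objective. The test may also reject more often than 5% when there is no relationship, so that a false finding would be reported beside a claim of 90% power.

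**Working it through.** **Inputs.** r = 0.50, two-sided 5%, power about 90%, N = 48, 12 teams of four (section 9.2). One performance value per scale per team session (4.2.1, 4.3.4, schedule in 4.4.1). Stress per participant (7.2). The protocol gives no within-team ICC of stress, so the ICC values below are assumptions.

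**1. The plan's own figure, with independent pairs.** By Fisher's z, n = ((z₀.₉₇₅ + z₀.₉₀)/atanh(r))² + 3.
- Pairs needed for 90%: ((1.960 + 1.282)/0.5493)² + 3 = 37.8, so 38.
- Power at 48: Φ(0.5493 × √45 − 1.960) = Φ(1.725) = 95.8%. A simulated t-test gives 96.1%.

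So 48 with about 90% does not reproduce. It would match r = 0.45 at 90% (48), roughly r = 0.50 at 95% (47), or 38 inflated for 20% loss (38/0.80 = 47.5, so 48). None of these is stated.

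**2. If 0.50 is the team-level correlation.** With one stress value and one score per team, n = 12.
- Power: Φ(0.5493 × √9 − 1.960) = Φ(−0.312) = 37.8%. A simulated t-test gives 40.0%.
- Correlation needed for 90%: tanh(3.242/3) = 0.79. For 80%: tanh(2.802/3) = 0.73.

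**3. If 0.50 is the individual-level correlation.** Four members share one score, and the variance of team-mean stress is (1 + 3·ICC)/4 of the individual variance. Hence r_individual = r_team × √((1 + 3·ICC)/4), so r_team = 0.50/√((1 + 3·ICC)/4). Effective N for one session is about 48/(1 + 3·ICC). Power below is for a test on 12 team means.

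| Assumed ICC | Effective N | Implied r_team | Power, Fisher z | Power, simulated t-test |
|---|---|---|---|---|
| 0.1 | 36.9 | 0.88 | 98% | 99% |
| 0.2 | 30.0 | 0.79 | 90% | 92% |
| 0.3 | 25.3 | 0.73 | 79% | 83% |
| 0.5 | 19.2 | 0.63 | 61% | 65% |

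At ICC 0 the implied team-level correlation is 0.50/√(1/4) = 1.00, the maximum possible. At ICC 1 effective N is 12 and the case becomes step 2.

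**4. Type I error of a Pearson test on 48 person rows.** Simulating 12 teams of four with a shared score and no true relationship gives rejection rates of about 5% at ICC 0, 9% at 0.1, 12-13% at 0.2, 16% at 0.3 and 23% at 0.5. The same simulation with one row per team stays near 5% throughout.

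**The case against.** The strongest objection concerns the level of r. Section 9.2 speaks of subjects, and stress is measured on each of them, so reading 0.50 as an individual-level correlation is at least as natural as the team-level reading. On that reading a 12-team test reaches about 90% at an ICC of 0.2 and more below it. This stands. A reader might infer that true power is simply about 40%; the documents do not support that, because they fix neither the level of r nor an ICC. The individual-level reading is demanding, however. For about 90% power or more, team-mean stress must correlate at 0.79 or above with team performance, and the protocol offers no basis for that.

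Two further inferences go too far. One is that the study yields only 12 performance values. Twelve is the count per scale per session; there are 72 team sessions, although they come from 12 independent teams and 54/72 = 75% belong to Group 1. The other is that 9.1.2 prescribes stacking all 288 person-sessions. It does not state the row layout, and correlations by session or by status fit its wording. The 48-row layout is what the sample size implies. Stacking sessions without a team effect would raise the error rate further, but by how much depends on variance shares that the protocol does not give.

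It can also be said that section 9.1.3 foresees linear mixed models over all sessions. That is true, but they are offered tentatively, for changes in performance scores, and they do not replace the correlation in 9.1.2.

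**Conclusion.** The sample size statement is wrong as written, in two separate ways. First, for independent pairs the arithmetic is off: 38 suffice for 90%, and 48 give about 96%. This error is conservative. Second, the pairs are not independent, and this matters more. The independent units are 12 teams, and effective N for one session lies between 12 and 48.

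The size of the loss is conditional. Power is about 38-40% if 0.50 is a team-level correlation. If it is individual-level, power runs from about 98% to 61% over assumed ICCs of 0.1 to 0.5. All these figures are for a one-session test on 12 pairs; none is the power of a model using all 72 team sessions.

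The inflated type I error of about 9-16% rests on assumed ICCs of 0.1 to 0.3 and on the 48-row layout. At an ICC of exactly zero there is no inflation. Team members share the room and the scenario, so zero is hard to assume.

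**What to change.** In section 9.2, replace the 90% claim with a statement based on 12 teams. It should say whether r = 0.50 is between individual stress and the team score or between team-level stress and the team score, and give power over a stated ICC range. For a one-session test on 12 pairs, this is about 38-40% at a team-level r of 0.50, and 90% only for a team-level |r| of about 0.79 or more.

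In section 9.1.2, replace the simple correlation across persons with an analysis that respects teams: team-session performance regressed on team-mean or leader stress, session number and group, with a random team intercept and small-sample degrees of freedom. Report the slope with its 95% confidence interval. Correlations by professional status should use one row per team, and analyses within a group should acknowledge that they rest on six teams.

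The cost is a less favourable, conditional power figure and slightly more analysis work. No participants or data are added.

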### **9.3. Degree of statistical significance**

A *p* score < 0.05 will be considered as statistically significant

### **9.4. Statistical criteria for study termination**

No statistical criterion for study can be defined because no intermediate statistical analysis is foreseen.

### **9.5. Method for considering missing, unused or invalid data**

All the information required by the protocol must be recorded, and an explanation must be provided for any missing, unused or invalid data.

### **9.6. Management of potential analysis modifications**

Any deviation from the statistical analysis scheme will be clarified and justified in the final analysis report.

## **10. RIGHT OF ACCESS TO DATA AND DOCUMENTS SOURCE**

### **10.1. Access to data**

According to the BPC:

- The sponsor is commissioned to obtain an agreement from all the parties involved in research so as to guarantee direct access to all the localities, data sources, document sources and reports, for the purpose of quality control and audit by the sponsor.
- The investigators will provide biomedical research personnel in charge with the follow-up, quality control and audit, all documents and individual data strictly necessary for this control, according to current legal and statutory measures (articles L.1121-3 and R.5121-13 of France's Public Health Code - "*Code de la santé publique*").

### **10.2. Source documents**

Source documents being defined as any original document or object allowing to prove the existence or exactness of data or facts recorded during study, will be kept during 15 years by the investigator.

### **10.3. Confidentiality concerning data**

In conformity with the dispositions pertaining to the confidentiality of data that can be accessed by biomedical research personnel in charge with the follow-up, quality control and audit (article L.1121-3 of France's Public Health Code - "*Code de la santé publique*"),

in conformity with the dispositions pertaining to the confidentiality of information, notably; the nature of experimental medicines, trial studies, participants who lend themselves to experimentation and obtained results (article R. 5121-13 of France's Public Health Code - "*Code de la santé publique*"),

all persons having direct access to such data and information will take all the necessary precautions to insure the confidentiality of information relative to the experimental medicines, to study trials, participants who lend themselves to experimentation (notably with regards to their identity) as well as to obtained results.

These persons, similarly to the investigators themselves, are bound by professional secret (according to conditions defined in articles 226-13 and 226-14 of France's Penal code).

During the biomedical research study, or upon its termination, all data collected on the persons who lend themselves to experimentation and passed on to the sponsor by the investigators (or all other specialized speakers), will previously have been made anonymous.

Under no circumstance will the participants' names or addresses appear clearly.

Only participants' name and surname initials will be recorded, followed by a code number appropriate for the study, indicating the participants' order of inclusion.

The sponsor will make sure that every person who lends himself to research experimentation will have previously granted written consent, allowing for access to personal data, and strictly necessary for quality control of the study.

